## Methods

The focus of this project is to develop and test the feasibility of a novel technology-based BGE to facilitate timely adherence to evidence-based guidelines and bolster consistent clinical decision-making. The team will develop and evaluate a technology-driven implementation strategy (the BGE) that facilitates the uptake of evidence-based guidelines for management of sTBI at the bedside (aim 1). We will then determine the feasibility of incorporating the BGE in the ICU environment (aim 2). This will include evaluation of the extent of adaptation of the BGE that is required at each of three participating ICUs. Feasibility testing will yield real world practice identification of site-specific barriers and facilitators to implementation of the BGE. More information for each step in will be described in the following section.

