#### Evaluating the BGE’s initial acceptability

After the BGE has been designed, we will present it to ICU team members from all three sites and gauge initial BGE acceptance. Finally, we will use focus groups with ICU team members to assess acceptability and suggested improvements for the BGE [53]. These measures and processes will be further explained below.

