#### Data collection and data analysis

##### Capturing the ICU environment and culture

Staff observations and interviews

Additionally, acceptance of the innovative BGE will be gauged by a collection of qualitative input from users [56, 57]. Data will be collected in separate sessions at each of the three clinical sites and will be analyzed using the grounded theory qualitative method [58].

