##### Evaluating the BGE’s initial acceptability

Technology Acceptance Evaluation Model

All quantitative data will be managed and analyzed using the R statistical computation system [59]. As the questionnaire measures—perceived ease of use, efficacy, and intention to use/trust—have a skewed distribution, we specify an ordered logistic model [10]. The dataset also has a multiply-aggregated structure, as participants are nested within their group’s session, and sessions are nested within clinical sites. To address the violation of independent-observation assumption, we apply a three-level mixed model to the data analysis as follows:
$$ {\displaystyle \begin{array}{ccc}P& Q& R\\ {}{}^{ln}{\left({}^Y ijk\right)}^{=\gamma }{000}^{+}{\sum}^{\gamma }p00{\left({}^X\right)}_{pijk}& {}^{+}{\sum}^{\gamma }0q0{\left({}^S\right)}_{qjk}& {}^{+}{\sum}^{\gamma }00r\left({}^W\right){{{}_{rk}}^{+}}^u00{k}^{+r}0j{k}^{+e} ijk\\ {}p=1& q=1& r=1\end{array}} $$where *ln(Y*_*ijk*_*)* is the outcome variable of interest for the *i*th participant working in the *j*th session from the *k*th site, *(X)*_*pijk*_ are *P* participant-level variables, *(S)*_*qjk*_ are *Q* session-level variables, *(W)*_*rk*_ are *R* site-level variables, *u*_*00k*_ is a random effect for the *k*^*th*^ site, *r*_*0jk*_ is a random effect for the *j*th session conducted in the *k*th site, and *e*_*ijk*_ is a residual term. Many individual-, session-, and site-level characteristics are coded as dichotomous variables. As such, the exponent of estimated coefficient exp (*γ*) for a dichotomous variable indicates percentage difference between groups on the level of technology acceptance. These effects, in conjunction with statistical significance testing, help discern barriers and facilitators of the implementation of BGE, which will be incorporated into the BGE’s design to optimize functionality and acceptance.

Perceived Attributes of eHealth Innovations Questionnaire

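### With only three sites, the planned site random effect is uninformative or unidentified, and significance tests of site characteristics are unreliable

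*Protocol article*

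**What the plan says.** The model is set out under Aim 1 of the protocol article, Evaluating the BGE's initial acceptability, Technology Acceptance Evaluation Model. Because the questionnaire scores are expected to be skewed, "we specify an ordered logistic model". Participants are nested in sessions and "sessions are nested within clinical sites". The article then states: "To address the violation of independent-observation assumption, we apply a three-level mixed model to the data analysis as follows". The displayed equation has participant-, session- and site-level covariates (P, Q and R of them), a random effect u_00k for site, a random effect r_0jk for session, and a residual. R is not given. Many covariates at all three levels are said to be dichotomous.

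The use of the coefficients is stated directly below the equation: "These effects, in conjunction with statistical significance testing, help discern barriers and facilitators of the implementation of BGE", and the results are to feed into the design of the bedside guideline engine (BGE).

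The number of sites is fixed in several places. Methods: "This will include evaluation of the extent of adaptation of the BGE that is required at each of three participating ICUs". Aim 1 procedures: "we will present it to ICU team members from all three sites and gauge initial BGE acceptance". Aim 1 data collection: "Data will be collected in separate sessions at each of the three clinical sites".

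Under Aim 2 the questionnaire is given again in simulation and during clinical implementation. The clinical implementation section says that its quantitative data will be analysed by the methods already described.

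**The concern.** A random effect for site, and any test of a site characteristic, draws its evidence from the number of sites and not from the number of staff. Three sites give three independent pieces of information at that level. Any dichotomous site variable that varies over three sites splits them one against two, so it is the same column as an indicator for a single site. It cannot be separated from anything else that is particular to that site. For example, Limitations mentions one participating ICU in an adult trauma center; a unit-type variable would simply label that ICU.

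When the site variance is estimated at zero, the model treats sessions and staff within a site as independent evidence about the site's trait. The dependence that the model was chosen to handle is then not handled at site level. What is at stake is the design work: a chance difference between one site and the other two could be read as a barrier or facilitator and built into the BGE.

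**Working it through.** The article gives no sample size, alpha, ICC or test type for this model, so there is no stated figure to reproduce.

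**Inputs from the article.** Three sites; participants in sessions in sites; ordered logistic model; site and session random effects; R site-level covariates, mentioned in the plural; significance testing.

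**Assumptions not in the article.** Two-sided 5% level; 4 sessions per site and 6 staff per session; session ICC 0.05; site ICC from 0 to 0.20; five response categories; one dichotomous site covariate (one site against two) with no true effect.

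**Step 1: degrees of freedom at site level.** df = 3 − 1 − R.
- R = 0: 2 df.
- R = 1: 1 df.
- R = 2, non-redundant: 0 df. The intercept and the two covariates fit the three sites exactly, so u_00k is not identified.
- R = 3: the third covariate is collinear with the others.

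**Step 2: precision of the site variance.** Take the best case, in which site means are observed without error. The 95% interval is the estimate times df/χ²(0.975) to df/χ²(0.025).
- 2 df: 2/7.378 = 0.27 to 2/0.0506 = 39.5 times the estimate.
- 1 df: 1/5.024 = 0.20 to 1018 times the estimate.

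**Step 3: reference distribution.** With one site covariate, a valid test on the three site means is a t test on 1 df. Its critical value is 12.71, not 1.96, and its simulated size was 5.0%. If 1.96 is used when site variance dominates, the false-positive rate tends to 1 − (2/π)·arctan(1.96) = 30.0% with a REML variance. With an ML variance (divisor 3 instead of 1) it tends to 1 − (2/π)·arctan(1.96/√3) = 46.1%.

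**Step 4: simulation of the ordinal model.** 2,000 data sets per setting, cumulative-logit model with both random effects, fitted by maximum likelihood with Gauss-Hermite quadrature. On the logit scale the true site SDs were 0, 0.43, 0.62 and 0.94.

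| Site ICC | Wald false positives | Likelihood-ratio false positives | Site SD estimated below 0.1, one site covariate | Same, no site covariate |
|---|---|---|---|---|
| 0 | 6.3% | 4.6% | 92% | 79% |
| 0.05 | 15.0% | 10.6% | 79% | 56% |
| 0.10 | 21.0% | 14.8% | 69% | 42% |
| 0.20 | 25.8% | 18.0% | 54% | 27% |

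The Monte Carlo standard error at 15% is √(0.15 × 0.85/2000) = 0.8 percentage points. Seven fits at ICC 0.20 gave no standard error and are left out of that Wald rate.

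**Step 5: cross-check in a linear three-level model.** 200,000 runs, same layout. At site ICC 0.05, 0.10 and 0.20 the z test rejected in 12.7%, 16.8% and 21.5% of runs with REML, and in 19.8%, 26.0% and 33.2% with ML. The direction and order of size agree with Step 4.

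**Step 6: two site covariates (saturated), linear model, site variance set to zero.** False positives ran from 20% to 43% (REML) and from 26% to 49% (ML) over site ICC 0.05 to 0.20.

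**The case against.** Much of the case on the other side stands.

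- **Purpose.** This is development and feasibility work. The coefficients only help to discern barriers and facilitators; they do not decide the design. Observations, interviews and group model building at each site, focus groups that explain the questionnaire results, and a simulation round before bedside use all stand alongside. A false site coefficient would be one signal among several. This lowers the severity. It is not a full safeguard, because the focus groups are there to explain and expand the quantitative findings, so a spurious one may be explained and not challenged.
- **Missing detail.** Alpha, the choice of Wald or likelihood-ratio test, the degrees-of-freedom method and the list of covariates may properly sit in an analysis plan that is not shown. The false-positive rates depend on those choices. The structure does not: a site random effect with tested site covariates on three sites is fixed in the article. A 1-df test would hold the level but have almost no power.
- **Stronger readings.** A reader might infer that the site variance can never be estimated. That is literally true only with two or more non-redundant site covariates, which the plural wording suggests but does not fix. A reader might also infer that every site test is far above 5%. The excess needs real variation between sites and large-sample tests; without such variation the ordinal rates are about 6% and 5%. Finally, a reader might take the whole acceptance analysis to be invalid. Participant- and session-level effects were not examined, and no harm to them is shown.

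**Conclusion.** The concern holds for the site random effect u_00k and the tests of site-level covariates, and only for those. With at most one site covariate, the site variance is practically uninformative. With two or more non-redundant covariates it is not identified. Under the assumptions listed in the working, a nominal 5% test of one site characteristic gives about 15% to 26% false positives (Wald) or 11% to 18% (likelihood ratio) over site ICC 0.05 to 0.20.

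These rates rest on assumed ICCs, cluster sizes and test type, none of which the article states. The degrees-of-freedom argument needs only the count of three sites. It should be fixed, but it is not critical: the consequence is possibly misdirected design refinement, not a false conclusion about efficacy or safety.

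**What to change.** In the technology acceptance model, enter site as a fixed factor (two indicators) and remove u_00k and the site-level covariates. Keep the session random intercept and the participant- and session-level covariates. Report the differences between the three sites with confidence intervals. Interpret them through the planned observations, interviews, group model building and focus groups, and do not test site traits for significance. Apply the same change where the model is reused in Aim 2.

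The intervals should allow for the small number of sessions. In the linear analogue with 12 sessions and no true site difference, a z test of one site against another rejected in 8.1% of runs (REML), and a t test on 12 − 3 = 9 df in 5.0%.

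The cost is a change of wording. What is lost is statistical generalisation beyond the three sites and a coefficient for each site trait; three sites cannot support either.

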### Aim 2: Determine the feasibility of incorporating the BGE in the ICU environment

#### Study population, subjects, and recruitment

In aim 2, we will test the feasibility of incorporating the BGE into clinical practice. We will prospectively enroll 36 pediatric patients with sTBI in the ICU from the three proposed trauma centers (approximately 12 patients per clinical site) during the 24-month period. This sample size was selected based on feasibility and practical considerations, including the number of patients typically diagnosed with sTBI. Pediatric patients with sTBI (measured as a Glasgow Coma Scale score of < 8) admitted to the ICU at each clinical site will be screened for participation. Inclusion criteria for pediatric patients are as follows: (1) age 0–17 years, (2) accidental or non-accidental sTBI, and (3) placement of an intracranial monitoring device for clinical care. In the final stages of feasibility testing, written informed consent from the patient’s parents or legal guardian will be obtained by the research team before testing of the BGE, and safety measures will be in place to assure testing of the BGE does not compromise patient care. Given the low potential risk to human subjects and the challenges encountered when seeking written informed consent shortly after children are admitted to the ICU with sTBI, we will request the option of delayed written informed consent (up to 48 h) for cases when delaying consent is necessary (e.g., if parents are not reasonably available at the time of admission). For patients who choose not to participate in our feasibility testing, consent for prospective data collection from the medical record will be obtained. The data will be used for initial exploration of penetration of the BGE into clinical practice.

#### Procedures, instruments, and design

##### Feasibility testing: patient simulation

Once the BGE has been developed, we will introduce the BGE to a multidisciplinary group of ICU clinicians representing all clinical sites. We will use an adaptation of a previously described simulation module for trauma and critical care patients [62] to conduct the patient simulation using resources from the Sigh Pediatric Simulation Center at St. Louis Children’s Hospital, St. Louis, MO. We will then reapply the Perceived Attributes of eHealth Innovations questionnaire and the Technology Acceptance Evaluation Model (*time point 2*) and capture qualitative user input regarding the BGE in the simulation environment. This approach will inform evaluation and adjustment of the BGE and will assist with final configuration prior to bedside feasibility testing at the clinical sites.

Feasibility testing: clinical implementation

After being tested in a patient simulation environment and revised accordingly, we will conduct feasibility testing in our three clinical sites. Clinical implementation will be bolstered using an implementation facilitator (IF), as well as trainings for clinical staff.

Implementation facilitator

Feasibility testing at each clinical site will be conducted with assistance from a Pediatric Neurocritical Care Program implementation facilitator (IF). The IF will assure adequate dissemination of the knowledge needed for users to understand and use the tool. This will occur through the collaboration with local multidisciplinary stakeholders (i.e., each ICU’s physician and nursing leadership and bedside care providers) and tangible implementation goals with respect to uptake and fidelity. The goals include use of the BGE for bedside decision-making, including incorporation of evidence-based care recommendations. The IF will also lead the team as they set goals and work through the stages of the innovation decision process [63]. The incorporation of an IF has previously used when implementing new protocol and technologies [64]; however, it is still uncommon in acute care settings like the ICU. Providing expertise on implementation and dissemination will foster success and ease of adoption.

Training

Training will be provided to all users with initial emphasis on a subset of clinicians (charge nurses and ICU attendings), assuring a trained user will be available at all times to coach clinicians during the bedside feasibility testing. The IF, knowledgeable in the context and workflow of the participating ICUs, will work closely with the Washington University Dissemination and Implementation Research Core to apply a training program using a template developed by the State Implementation and Scaling-up of Evidence-based Practices (SISEP) Center at the University of North Carolina [65]. This approach emphasizes training and coaching on new skills that are necessary for effective use of innovations. Training will include videos developed in collaboration with Moberg ICU Solutions. The education process will continue until all providers are trained on BGE use, providing coaching, or advising and assisting through completion of the evaluation, to capture immediate feedback and increase fidelity [63, 64, 66, 67].

Clinician interviews

Finally, we will evaluate the BGE’s practicality (predicted cost, burden and benefit to ICU team), integration (extent of use and impact on other activities in the ICU), and expansion (perception of how expanded deployment would work) [68]. Information will be obtained through semi-structured interviews of clinicians (nurses, respiratory therapists, attending physicians and physicians in training) and hospital administrators [67, 69].

#### Data collection and data analysis

##### Feasibility testing: patient simulation

Perceived Attributes of eHealth Innovations Questionnaire

Data extracted will be analyzed using the same methodology as aim 1.

Cognitive interviewing

Use a think-aloud cognitive interviewing to obtain in vivo thoughts and reactions in the simulation environment [70].

##### Feasibility testing: clinical implementation

During the feasibility testing phase, the Technology Acceptance Evaluation Model and the Perceived Attributes of eHealth Innovations questionnaire will be distributed again [54, 55]. Similarly, cognitive interviewing will be used after implementation. Quantitative and qualitative data will be analyzed using the same methodology as previously described.

#### Trial status

Study procedures have been approved by the Institutional Review Board at Washington University in St. Louis and the University of Missouri, Kansas City. Data collection and BGE designing are ongoing at the time of submission of this manuscript (July 2019).

## Discussion

To improve clinical outcomes for children with sTBI, the best available evidence-based care must be more effectively tested and consistently applied in real-world practice. This study will develop and evaluate an innovative implementation strategy (a technology-based BGE) to facilitate timely delivery of evidence-based care of children with sTBI. The overall objective is to reduce fragmentation between evidence-based guideline information and actionable patient data, a barrier that typically stands in the way of fidelity to guidelines. If successful, this approach will also prove useful for implementation of guidelines for treatment of other complex and time sensitive conditions in the ICU environment.

Our innovative approach will incorporate state of the art technology and input from real world practice at three pediatric trauma centers. Our approach proposes significant change in the way care is delivered to children with sTBI by making evidence-based care easier for providers to apply in a timely fashion. The BGE will incorporate real-time feedback from the patient’s physiology through the CNS monitor while giving providers access to high resolution data trends; the BGE will then link these data to an evidence-based guideline with the goal of improving decision-making and timely delivery of therapy. The BGE will be built with capacity to efficiently incorporate new evidence as it becomes available. Ultimately, we anticipate this strategy will create a sustainable approach to efficient and consistent care for critically ill children with sTBI.

If successful, this approach may prove useful for the implementation of evidence-based guidelines in other settings where time sensitive, complex care is provided (e.g., other ICU conditions, the emergency department, or battlefield). Other ICU conditions that may benefit from this approach include management of nutrition, sedation/analgesia administration, treatment of life-threatening infections, and prevention of hospital acquired conditions. The innovation developed in this project may also contribute to the design of a future model of care that can adapt to different institutions and have a sustained impact on outcomes.

### Limitations

There are limitations to this project that should be noted. First, though previous and emerging evidence supports the effectiveness of guideline-based care in adults and children with sTBI, better understanding of the pathophysiology and effectiveness of specific interventions is needed. Additionally, in this 2-year project, it is possible that the number of patients in the feasibility testing phase will not be sufficient to adequately test the BGE. The participating adult trauma center ICU may have access to fewer pediatric patients, but since pediatric trauma patients can receive care at adult trauma centers, we believe it is important to gain knowledge from our feasibility testing in a non-pediatric trauma center/ICU environment. Given that we are using process-of-care outcomes as our metrics, we anticipate patient accrual will not be a significant limitation. Future studies are being planned to test the impact of the BGE on patient outcomes.

## Conclusions

Previous research has highlighted the need for an innovative implementation strategy to scale up and sustain guideline-based care. As such, we hope to use the BGE to improve outcomes in children with sTBI by facilitating timely, consistent, and sustained application of evidence-based care in routine practice. Our long-term goal is to develop and rigorously test an implementation strategy that fits the realities of clinical practice and individual patients and contributes to sustained implementation of guideline-based care for children with sTBI. This innovative proposal enables us to take the first step in this long-range implementation program.

Development of the BGE meets the broad need to decrease unnecessary variation in care and improve compliance with desired therapies, highlighting the relevance and generalizability of our approach to the wider ICU population [71]. We believe the proposed BGE will improve the application of adaptable guideline-based TBI care to meet the needs of individual ICU environments and patients. Additionally, this implementation strategy might guide the successful adaptation of our approach at other institutions. In a future comparative effectiveness clinical trial, we will propose scaled implementation of the BGE anticipating this approach will be superior to traditional care in translating knowledge into practice, positively impacting outcomes for children with sTBI.

